#### Statistical analysis

Data analysis will be performed in consultation with [name] in CSTARS. The primary conclusions of this project will be based on analyses conducted under the principal of intention to treat. All randomised patients will be analysed in the groups to which they are originally allocated to regardless of whether they actually received the intended treatment or not. Missing primary outcomes will be assumed to be missing at random and will not be considered in the primary analysis.

Primary analysis of the effect of functional exercise will incorporate continuous variables which are expected to be normally distributed. These will be presented as mean and standard deviations and will be assessed using t tests at different time points i.e. at 12 weeks and again at 18 weeks. If the data is not normally distributed it is planned to use the non parametric Wilcox on signed ranks test.

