**Methods/design:**

This will be a single blind multi centre randomized control trial with two arms. Seventy subjects post primary total hip arthroplasty will be randomized into either an experimental group (n=35), or to a control group (n=35). The experimental group will attend a functional exercise class twice weekly for a six week period from week 12 to week 18 post surgery. The functional exercise group will follow a circuit based functional exercise class supervised by a chartered Physiotherapist. The control group will receive usual care. The principal investigator (BM) will perform blinded outcome assessments on all patients using validated measures for pain, stiffness, and function using the Western Ontario and Mc Master Universities Osteoarthritis index (WOMAC). This is the primary outcome measurement tool. Secondary outcome measurements include Quality of life (SF-36), 6 min walk test, Visual Analogue Scale, and the Berg Balance score. The WOMAC score will be collated on day five post surgery and repeated at week twelve and week eighteen. All other measurements will be taken at week 12 and repeated at week eighteen. In addition a blinded radiologist will measure gluteus medius cross sectional area using real time ultrasound for all subjects at week 12 and at week 18 to determine if the functional exercise programme has any effect on muscle size.

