### Procedure

Preliminary screening will be carried out at the pre-assessment clinic by the principal investigator (BM). Following a standard interview process patients will be given a written description of the study and information with regard to the exercise class commitment involved. A screening record will be kept to document criteria eliminating those deemed to be ineligible. All patients will all be assessed using the WOMAC questionnaire on day 5 prior to discharge and they will be randomized to one of two treatment groups. The functional exercise intervention begins at week 12 and all patients will complete the Primary and Secondary outcome assessments at this point. All assessments are repeated for both groups at week 18. Patients allocated to the functional exercise class will attend a six week functional exercise programme twice weekly from week 12 to week 18. The control group will receive the standard usual post surgery care as outlined in the patients’ information booklet given to all patients on admission. This care is given to all patients post surgery by the Physiotherapist working on the ward. This study is one comparing usual treatment with an intervention of functional exercise. All patients randomised to the usual care group will be offered the chance to attend the exercise group at week 18 post evaluation.

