### Follow-up period

The duration of this research project is eighteen weeks from the date of surgery. All patients will complete the WOMAC questionnaire on discharge from hospital at day 5 and all outcome measurements will be repeated at week 12 and again at week 18. The outcome measurement assessments at week 12 and at week 18 will take place in Our Lady’s Hospital in Navan.

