#### Sample size

The power calculations were based on the physical function subscale of the WOMAC questionnaire. The minimal clinical difference on the WOMAC questionnaire has been established in the literature at −10.4 with the standard deviation of scores on the instrument at 13.6 [20]. The sample size was then calculated requiring a power of 80% in a two tailed test with a significance level of .05. The effect size was calculated at 10.4/13.6. It was .764 or a mod/large effect size. The sample size required was then calculated at 27 patients in each group or 54 in total. This would increase to 60 patients in total allowing for 10% attrition.

Consideration of the power calculations based on both the Berg balance score and the SF36 short form health survey, similar numbers are required. Using minimal detectable change scores and standard deviations from the literature [25] sample sizes at 80% power and .05 significance in a two tailed test were calculated at 70 subjects in total for the Berg Balance score and 54 subjects for the SF36 respectively. Therefore 70 subjects in total or 35 in each group would allow for 10% attrition for all outcome measurement tools.

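### Assuming missing at random does not by itself justify leaving out patients without the primary outcome and running t tests, and the exclusion conflicts with analysing all randomised patients

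*Protocol article*

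**What the plan says.** All the governing statements are in the protocol article, section Statistical analysis.

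- Principle: "The primary conclusions of this project will be based on analyses conducted under the principal of intention to treat".
- Who is analysed: "All randomised patients will be analysed in the groups to which they are originally allocated to", whether or not they received the intended treatment.
- Missing data: "Missing primary outcomes will be assumed to be missing at random and will not be considered in the primary analysis".
- Test: the continuous outcomes "will be assessed using t tests at different time points i.e. at 12 weeks and again at 18 weeks". No covariate, repeated-measures model or imputation is named, and the section does not say whether final scores or changes are compared.

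Earlier scores on the same instrument will exist. The abstract states: "The WOMAC score will be collated on day five post surgery and repeated at week twelve and week eighteen". The Follow-up period section confirms the first of these: "All patients will complete the WOMAC questionnaire on discharge from hospital at day 5". The Sample size section plans for 10% attrition.

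**The concern.** There are two mismatches.

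**Analysis set.** Keeping patients in their allocated arm is one part of intention to treat; including all of them is another. The section promises both, and the next sentence withdraws the second. Reading the exclusion as merely a decision not to impute changes nothing, because a t test drops a patient with no value.

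**Assumption and method.** Missing at random means that, given the observed data, missingness does not depend on the unobserved value. The observed data include arm and the day 5 and week 12 WOMAC. An analysis that relies on this assumption has to use those data. A two-sample t test conditions on arm alone. It needs something more: that loss is unrelated to outcome within arm, or that the selection cancels between arms.

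Unequal, score-related loss is conceivable here. Only the exercise arm has twelve classes to attend. Randomisation takes place long before week 12: the Procedure section puts it around day 5 ("All patients will all be assessed using the WOMAC questionnaire on day 5 prior to discharge and they will be randomized"), and Randomisation and allocation concealment puts it after written consent. Independent walking and the consultant's clearance at six weeks are judged later, so patients can be lost both before and after week 12. If loss selects on score differently by arm, the estimated effect of exercise shifts for reasons unrelated to exercise.

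**Working it through.** **The plan's own figure.** Inputs from Sample size: difference and SD "established in the literature at −10.4 with the standard deviation of scores on the instrument at 13.6", 80% power, two-sided 0.05.

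- n per arm = 2 × (1.96 + 0.84)² / (10.4/13.6)² = 15.7 / 0.585 = 26.8, so 27 per arm and 54 in total, as stated (28 per arm with the t distribution).
- 54 / 0.9 = 60, as stated.
- At 10% loss, 7 of the 70 planned patients have no outcome. With 31.5 per arm, power for 10.4/13.6 is still about 85%. The question is therefore bias, not power.

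**Bias formula.** Let z be the standardised week 12 score (higher is worse), ρ its correlation with week 18, and m the mean z among completers in an arm. If loss depends only on z, the bias of the completers' week 18 difference is

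bias = ρ × SD × (m_exercise − m_control).

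For change from week 12 (equal SDs), replace ρ by ρ − 1, which has the opposite sign. Adjusting for z removes the term.

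**Assumed mechanisms.** The article gives no ρ and no loss pattern. Take ρ = 0.5 to 0.7, loss in control unrelated to score (m_control = 0), and exercise loss higher above z = 0.84. There the normal tail area is 0.2005 and the density 0.2803. With loss probability h above the cut and l below,

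m_exercise = −(h − l) × 0.2803 / (1 − total loss).

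- *Severe, h = 0.60, l = 0.02.* Loss = 0.2005 × 0.60 + 0.7995 × 0.02 = 0.136. m = −0.58 × 0.2803 / 0.864 = −0.188.
- *Gentle, h = 0.30, l = 0.05.* Loss = 0.2005 × 0.30 + 0.7995 × 0.05 = 0.100. m = −0.25 × 0.2803 / 0.900 = −0.078.

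| Mechanism | ρ | Week 18 score: ρ × 13.6 × m | Change score: (ρ − 1) × 13.6 × m |
|---|---|---|---|
| Severe | 0.7 | −1.8 | +0.8 |
| Severe | 0.5 | −1.3 | +1.3 |
| Gentle | 0.7 | −0.7 | +0.3 |
| Gentle | 0.5 | −0.5 | +0.5 |

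Negative values favour exercise. In simulation with no true effect and 35 per arm, the type I error of the week 18 t test was about 6% to 8% under the severe mechanism and 5.6% under the gentle one at ρ = 0.7.

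**Other mechanisms.** These simulations used a logistic dependence on week 12 score (slope 1 per SD where loss depends on score) and ρ = 0.5 to 0.7. Bias was computed with a true effect of −10.4, and type I error with no effect.

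| Loss pattern | Bias of week 18 t test contrast (points) | Type I error |
|---|---|---|
| Unrelated to score within arm, 5% v 15% | about 0 | not run |
| Same mechanism, 10% in both arms | about 0 | about 5% |
| Same slope, 5% v 15% | −0.55 to −0.79 | not run |
| Score-dependent in exercise only, 10% in each arm | −0.62 to −0.87 | 5.7% to 6.1% |
| Opposite directions, 10% in each arm | −1.26 to −1.71 | 6.4% to 7.4% |
| Opposite directions, 20% in each arm | −2.36 to −3.35 | 9.8% to 15.4% |

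Adjusting for the week 12 score kept bias within 0.03 points in every row.

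**The case against.** **A reader might infer that the planned analysis is biased whenever data are missing at random, or valid only if they are missing completely at random.** Neither follows. Loss that depends on arm alone is not completely at random, yet it leaves the contrast unbiased, as does the same mechanism and rate in both arms. The right wording is that the analysis can be biased.

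**A reader might infer that the bias makes exercise look effective.** The article does not support a direction. It does not say whether final or change scores are tested, and under the same mechanism the change-score comparison errs against exercise. Nor does it say who would be lost. Stopping classes is not the same as missing the assessment: assessments are separate visits in Navan for both arms, willingness to attend twice weekly is an entry criterion, and controls are offered the classes after the week 18 evaluation. All of this stands, so the direction is conditional.

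**The severe mechanism is near-extreme.** A 30-fold ratio of loss (0.60 to 0.02) in one arm is a choice, and its 13.6% loss exceeds the planned 10%. This also stands, and is why a range is shown.

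**The intention-to-treat sentence may concern grouping only, with the exclusion openly declared next.** That makes the conflict milder, an available-case analysis loosely described. It does not remove it, because the sentence says that all randomised patients are analysed.

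**Detail may sit in an analysis plan not shown.** It may, but the article itself fixes the assumption, the exclusion and the test, so a later plan would have to reverse this text and not merely add to it.

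**Conclusion.** The point holds in a limited form. The stated analysis set conflicts with the stated exclusion, and missing at random does not by itself support t tests on completers.

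The consequence is possible bias, not certain bias. Under the assumptions shown (ρ 0.5 to 0.7, about 10% to 13% loss, score-dependent in the exercise arm only), it is about −0.5 to −1.8 points on week 18 scores. As a share of the 10.4-point target that is 0.5/10.4 = 5% to 1.8/10.4 = 17%, with type I error of about 5% to 8%. It is about +0.3 to +1.3 points if changes are tested. Larger values need opposite mechanisms and heavier loss than planned. The contradiction in the text is certain; the size and direction rest on assumptions. The bias is modest, but worth correcting because the correction is almost free.

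**What to change.** Make the primary week 18 comparison one that uses the WOMAC scores already collected, by either of these:

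- a likelihood-based repeated-measures model over day 5, week 12 and week 18, including every randomised patient with any WOMAC score, with the week 18 difference between arms as the primary contrast; or
- multiple imputation of week 18 from arm, day 5 and week 12, followed by a comparison adjusted for the earlier score.

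Both can use day 5 for patients lost before week 12, whom adjustment for an observed week 12 score alone would still drop. The calculations above tested only week 12 adjustment, not these fuller models.

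Reword the intention-to-treat sentence to match: patients are grouped as allocated, those with any WOMAC score contribute under missing at random, and any with none are counted and reported by arm. The covariance structure and any sensitivity analysis departing from missing at random can be left to the analysis plan.

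The cost is analysis wording and a standard software procedure. No visit, measurement or patient is added.

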### Primary hypotheses

A six week functional exercise programme from week 12 to week 18 in patients post total hip replacement will be more efficacious in improving pain, stiffness and function than the usual care programme.

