### Randomisation and allocation concealment

Following a standard interview at the pre assessment clinic, Patients will be given a written description of the study and information with regard to the exercise class commitment involved. They will also be given stamped addressed envelopes to post back written consent. Following obtainment of written consent random allocation using sequentially numbered envelopes to both groups will be carried out by a third party [name] (LBC) who is not involved in the study. The number sequence will be generated using a computer generated random number table generated by [name] and communicated directly to LBC. Subjects will be randomly allocated either to a functional exercise class from week 12 post op to week 18 or to a control group receiving usual post operative care. Allocation of patients to the treating therapists will be established by e mail contact from LBC to the Physiotherapist’s responsible for conducting the classes. These therapists have been identified previously. Patients will be asked not to discuss their group allocation and all blinded outcome assessment examinations will take place in Our Lady’s Hospital, Navan.

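### The primary analysis names t tests at weeks 12 and 18 but no single baseline-adjusted between-arm contrast, and its non-parametric fallback is a paired test

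*Protocol article*

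**What the plan says.** The Statistical analysis section of the protocol article describes the primary analysis of the exercise effect as applied to continuous variables that "will be assessed using t tests at different time points i.e. at 12 weeks and again at 18 weeks". It continues: "If the data is not normally distributed it is planned to use the non parametric Wilcox on signed ranks test". It names no covariate, change score or longitudinal model, and no other section adds one.

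The Procedure section fixes the timing: "The functional exercise intervention begins at week 12 and all patients will complete the Primary and Secondary outcome assessments at this point". It then states: "All assessments are repeated for both groups at week 18". For the WOMAC there is also an earlier measurement; according to the Abstract, "The WOMAC score will be collated on day five post surgery and repeated at week twelve and week eighteen".

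Under Primary hypotheses, the programme, run from week 12 to week 18, "will be more efficacious in improving pain, stiffness and function than the usual care programme".

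Allocation comes well before the classes. Under Randomisation and allocation concealment: "Following obtainment of written consent random allocation using sequentially numbered envelopes to both groups will be carried out by a third party".

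**The concern.** Three things do not fit together.

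- **The week-12 test.** It is listed as part of the primary analysis of the exercise effect, but no class has been held by then. The section does not say which time point decides the trial.
- **The week-18 test.** The hypothesis is about improvement over weeks 12 to 18, and a week-12 score is collected for every outcome. As written, a between-arm t test at week 18 makes no use of it. In a trial of this size, a chance difference at week 12 would pass in part into the week-18 result.
- **The type of test.** The signed ranks test compares paired values. It would match a within-arm comparison over time, not a comparison of two independent arms. If the t tests were also meant to be within arms, the trial would have no between-arm test of its hypothesis. If they are between arms, the fallback is the wrong test.

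At stake are a clear primary contrast, fixed before the data are seen, and precision that the planned data can supply at no cost.

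**Working it through.** **1. What each stated test can answer**

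| Reading of the t tests | Week 12 | Week 18 | Does the signed ranks fallback fit? |
|---|---|---|---|
| Between arms | Compares arms before any class | Valid comparison of arms, unadjusted | No |
| Within arm, paired | Change since day 5, which only the WOMAC has on every schedule given | Change since week 12 in each arm separately | Yes, but the arms are never compared |

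On neither reading is there a between-arm comparison adjusted for the week-12 score.

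**2. The plan's own sample size**

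The Sample size section gives the difference and SD as "established in the literature at −10.4 with the standard deviation of scores on the instrument at 13.6", with 80% power and two-sided alpha 0.05.

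n per arm = 2 × (1.960 + 0.842)² × (13.6/10.4)² = 26.8, so 27 per arm and 54 in total. With 10% attrition, 54/0.9 = 60. Both figures match the plan. This is the formula for an unadjusted comparison of two arms at one time point, which supports the between-arm reading for week 18.

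**3. Precision and power with and without adjustment**

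Inputs: difference 10.4 and SD 13.6 (Sample size section). Planned enrolment is 35 per arm; with 10% attrition, 35 × 0.9 = 31.5, taken as 31 and 32. The correlation r between week-12 and week-18 scores is not in the document, so 0.3 to 0.7 is assumed.

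- SE of the week-18 difference = 13.6 × √(1 − r²) × √(1/31 + 1/32), where r = 0 gives the unadjusted test.
- 95% CI half-width = t × SE, with t = 2.00 (61 degrees of freedom unadjusted, 60 adjusted).
- Power from the non-central t distribution with non-centrality 10.4/SE.

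| Analysis | SE | CI half-width | Power at 10.4 |
|---|---|---|---|
| Unadjusted | 3.43 | 6.9 | 0.85 |
| ANCOVA, r = 0.3 | 3.27 | 6.5 | 0.88 |
| ANCOVA, r = 0.5 | 2.97 | 5.9 | 0.93 |
| ANCOVA, r = 0.7 | 2.45 | 4.9 | 0.99 |

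**4. Validity of the unadjusted week-18 test**

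Simulation with 31 per arm and no treatment effect gave a type I error of 4.9% to 5.1% for r from 0 to 0.8. The test is sound over repeated randomisations.

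Conditional on an unlucky draw it is less comfortable. With 31 per arm the SE of the week-12 difference is 13.6 × √(2/31) = 3.45 points. An imbalance of 1.96 SE is 6.8 points, of which r × 6.8 carries into week 18: 2.0 points at r = 0.3 and 4.7 at r = 0.7.

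**5. If either time point counted as success**

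The chance of at least one false positive would be 9.5% at r = 0.3 and 8.3% at r = 0.7, instead of 5%. The plan does not state such a rule; it only leaves the deciding time point unnamed.

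**The case against.** The strongest reply is that the week-18 comparison needs no repair. In a randomised trial it is unbiased without adjustment, it keeps its 5% error rate, the sample size was calculated for exactly that test, and power at the planned effect is about 0.85 after attrition. All of this stands. A reader might infer that the primary analysis is invalid or the trial underpowered, for instance because an unadjusted test has only about 50% power for a 0.5 SD effect. The documents do not support that: the plan never uses 0.5 SD, and its own effect is 10.4/13.6, about 0.76 SD. The gain from adjustment is also modest if the correlation is low.

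A second reply is that the protocol plainly treats week 12 as before treatment (the Timelines section calls that testing pre-intervention), and nothing says a week-12 difference would be claimed as an effect. That also stands, so misuse of the week-12 test is a possibility, not a plan. It does not explain why the test is listed under the primary analysis of the exercise effect.

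A third reply is that week 12 is not a true baseline, because patients are randomised about three months earlier. They are asked not to discuss their allocation, which implies that they know it. A week-12 difference could therefore reflect knowledge of allocation or differential dropout as well as chance. This is correct and limits the remedy: adjustment for week 12 needs a statement of what is being estimated, and a sensitivity analysis.

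Finally, a condensed article may leave secondary models to a fuller plan. Hence adjustment of the secondary outcomes is only a recommendation here.

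**Conclusion.** The point holds in a limited form. The article fixes its primary method, and that method includes a week-12 test that cannot measure the classes, names no single deciding contrast, states no baseline-adjusted between-arm comparison, and pairs the t tests with a fallback for paired data. Whether the t tests are between or within arms cannot be settled from the text, although the sample size formula points to between arms.

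On that reading, the cost of leaving the analysis unadjusted is precision: a CI about 5% wider than necessary at r = 0.3 (6.9 against 6.5) and about 40% wider at r = 0.7 (6.9 against 4.9). These sizes rest on the assumed correlations, the plan's SD of 13.6, and 10% attrition from 35 per arm. They also take week 18 as the post-treatment visit, as the Abstract, Procedure and Follow-up period sections do; the different weeks given in Table 2 and in the WOMAC description are a separate matter to reconcile.

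This is a free improvement in precision and clarity.

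**What to change.** Amend the Statistical analysis section as follows.

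1. Name one primary contrast for each WOMAC measure: the between-arm difference at week 18, estimated by ANCOVA adjusted for the week-12 score of the same measure, with a 95% CI.
2. Report week-12 scores by arm descriptively, without a test of effect.
3. Replace the signed ranks fallback with a method for independent arms, either the rank-sum test or a rank-based ANCOVA.
4. State that, because week 12 is pre-treatment but post-randomisation, the estimate is the effect of the classes from week 12 onwards.
5. Add a WOMAC sensitivity analysis adjusted for the day-5 score instead of the week-12 score. The day-5 score is taken at discharge, long before the classes.
6. Preferably use the week-12 adjustment for the secondary outcomes too.

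The cost is a change of wording before the statistician is unblinded. Every score needed is already scheduled, and neither the sample size nor the visits change.

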#### A priori defined subgroup analysis

Exploratory analysis on a subgroup of patients using real timed ultrasound to assess the size of gluteus medius in the non affected side will be carried out. This subgroup will be randomly selected from the main group following initial randomisation. It is planned to compare the size of the glut medius in the non affected side with the affected side at week 12 and again at week 18. This data is expected to also to be normally distributed and will be assessed using t tests at the various time points. The results of any subgroup analyses will be reported and submitted for publication soon after the primary publication.

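### The only non-parametric fallback for the primary analysis is a paired test (Wilcoxon signed-rank), but the primary comparison is between two independent randomised arms

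*Protocol article*

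**What the plan says.** The design is a two-arm parallel trial. The abstract states: "Seventy subjects post primary total hip arthroplasty will be randomized into either an experimental group (n=35), or to a control group (n=35"). The section on randomisation and allocation concealment describes individual allocation with no matching: "Subjects will be randomly allocated either to a functional exercise class from week 12 post op to week 18", or to a usual-care control group. The primary hypothesis is a contrast between those arms, namely that the programme "will be more efficacious in improving pain, stiffness and function than the usual care programme".

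Under Statistical analysis, the principle is intention to treat: "All randomised patients will be analysed in the groups to which they are originally allocated". Missing primary outcomes are left out of the primary analysis. The continuous outcomes are expected to be normal and "will be assessed using t tests at different time points i.e. at 12 weeks and again at 18 weeks". The next sentence is the only alternative offered: "If the data is not normally distributed it is planned to use the non parametric Wilcox on signed ranks test". The split in the test's name is typographical; the reference to signed ranks is clear. The article mentions no rank-sum or Mann-Whitney test, and it does not restrict the fallback to within-patient comparisons.

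**The concern.** The signed-rank test works on one difference per pair. In this trial, pairs exist only within a patient (week 12 with week 18, or one hip with the other). A patient in the exercise arm has no partner in the control arm. If the fallback is triggered, an analyst who follows the text has two options:

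- force a pairing of unrelated patients across arms; or
- run a before-after test inside each arm.

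The first is arbitrary, and impossible with unequal numbers. The second does not test the primary hypothesis, and it risks crediting exercise with recovery that would have happened anyway. The trigger is plausible, because the primary outcomes are bounded WOMAC subscales (pain 0–20, stiffness 0–8, function 0–68), some of them short.

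**Working it through.** **1. Which comparison was the trial sized for?** Inputs from the Sample size section: difference 10.4, SD 13.6, and "The sample size was then calculated requiring a power of 80% in a two tailed test with a significance level of .05".

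- Two independent groups, normal approximation: n per arm = 2 × (1.960 + 0.842)² × (13.6/10.4)² = 26.8, so 27 per arm and 54 in total. This is the article's own figure. Allowing for 10% attrition, 54/0.9 = 60, also as stated.
- Independent-samples t test (noncentral t): 27.8, so 28 per arm.
- Paired or one-sample t test with the same standardised effect, 10.4/13.6 = 0.765: 15.5, so 16 pairs.

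The stated 27 per group matches an independent-groups comparison and not a paired one.

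**2. Signed-rank used between arms.** Planned size is 35 per arm; less 10% attrition this is 31.5, taken as 31.

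- *Unequal completers.* With 33 and 31, for example, there is no complete pairing and the test cannot be computed. Attrition is expected and missing outcomes are left out, so unequal numbers are likely.
- *Equal completers.* The p value depends on who is paired with whom. In one simulated normal data set (31 per arm, true difference 0.765 SD), 5,000 random pairings gave signed-rank p values from 0.00003 to 0.026. The rank-sum test gives a single p of 0.003.
- *Type I error.* For lognormal data (sigma 0.8, assumed), 31 per arm, no effect and arbitrary pairing, the signed-rank test rejects in about 4.6% of runs. The level is held.
- *Power* in the same assumed lognormal setting:

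| Shift of 0.6 applied on | Signed-rank, arbitrary pairing | Rank-sum |
|---|---|---|
| log scale | about 77% | about 81% |
| raw scale | about 67% | about 84% |

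Repeat simulations move these by one to two percentage points.

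**3. Signed-rank used within an arm, week 12 against week 18.** Assume no exercise effect, both arms improving by 0.4 SD, and a correlation of 0.6 between visits. The SD of change is √(2 × (1 − 0.6)) = 0.894, so the improvement is 0.4/0.894 = 0.447 SD of change. With 31 patients, the exercise arm is significant in about 65% of simulated trials. The arms are independent, so the chance that exercise is significant and control is not is 0.65 × 0.35 = 0.23.

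The documents give neither the recovery nor the correlation, so here is a range (31 per arm, no exercise effect):

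| Recovery, in SD of change | One arm significant | Exercise significant, control not, p(1 − p) |
|---|---|---|
| 0.30 | 36% | 0.36 × 0.64 = 23% |
| 0.50 | 75% | 0.75 × 0.25 = 19% |
| 0.76 | 98% | 0.98 × 0.02 = 2% |

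**4. Does the right test need more patients?** Under normality the rank-sum test has relative efficiency 3/π = 0.955, so it needs 27.84/0.955 = 29.2, or 30 per arm. Simulated power with normal data is about 0.77 at 27 per arm, 0.82 at 31 and 0.87 at 35. At the worst-case efficiency of 0.864 it needs 27.84/0.864 = 32.2, or 33 per arm. That is slightly more than 31 completers but within the 35 randomised.

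**The case against.** **The fallback may never be used.** The planned test is the t test, on outcomes expected to be normal, and a statistician is consulted. Two tests carry the Wilcoxon name, so this may be a slip that would surface as soon as the arms proved unequal. This stands, and it is why the point is moderate. It does not make the sentence correct.

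**The test may be meant only for within-patient change.** The text does not say so. The sentence directly follows the primary analysis of the exercise effect and is its only fallback. On this reading the between-arm comparison would have no fallback at all. Equally, nothing says that within-arm tests are intended: the t tests are specified at each time point. The 65% and 23% therefore describe what happens if an analyst takes that route, not what the plan prescribes.

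**Stronger readings a reader might infer, which the documents do not support:**

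- *That the between-arm use inflates false positives.* Under the null hypothesis, differences between unrelated patients from identical distributions are symmetric about zero. The level holds, as the 4.6% shows. The faults are non-computability, arbitrariness and lost power.
- *That the 23% should be read against a nominal 5%.* That is not the reference rate for the joint event of one arm being significant and the other not.
- *That the gluteus medius side-to-side comparison is also wrong.* The subgroup section says: "This data is expected to also to be normally distributed and will be assessed using t tests at the various time points". That term includes the paired t test. Leaving out the word paired for an exploratory analysis is detail an article may leave to the fuller document.

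A separate analysis plan may exist. That would excuse an omission, but here the article names a specific test that does not fit its design.

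**Conclusion.** The point holds and is of moderate severity. The article's one stated remedy for non-normal primary outcomes is a paired test, while its hypothesis, allocation and sample size all describe independent arms. That mismatch follows from the text alone and needs no assumption.

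The sizes do rest on assumptions. The power loss of about 4 to 17 percentage points depends on the assumed lognormal shape and on the scale of the shift. The within-arm figures depend on assumed recovery and correlation. Nothing here affects the primary t test or the sample size, and the fault has no effect unless normality is rejected.

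**What to change.** In the Statistical analysis section, name the Wilcoxon rank-sum (Mann-Whitney) test as the fallback for between-arm comparisons. State that the signed-rank test is kept only for within-patient comparisons.

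The cost is one or two sentences of wording, to be settled before the data are analysed. No data collection, patient procedure or sample size changes: the planned 70 stays roughly adequate for the rank-sum test, with power about 0.82 at 31 per arm under normality.
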